# Introduction

## Study Background

Attention Deficit/Hyperactivity Disorder (ADHD) substantially burdens affected children, parents and society. It is well-known that early drug therapies can change trajectories and reduce individual, family and societal burden, and cost‐effectiveness studies have focused on available drug therapies and less on non‐medical interventions. Children with neurodevelopmental problems such as ADHD are at higher risk of experiencing abuse and/or neglect so it is crucial that their families receive targeted support. As a first line of treatment, NICE guidelines recommend a group parenting intervention, the effectiveness of which has been proven. It is however unclear whether an intervention designed specifically for families of children with a diagnosis will be more effective and cost effective.

Parents In Control (Parents InC / PInC) offers support designed specifically for parents of children with ADHD. The current best evidenced alternative is Incredible Years (IY). What needs to be determined is whether PInC i) is at least as effective as IY in impacting children’s behaviour outcomes; ii) is cost‐effective; and iii) offers something unique in terms of parenting self‐competence and quality of life.

## Study Objectives

This study is a feasibility trial aiming to address the following research questions:

1. Are parents of children recently diagnosed with ADHD willing to be randomised to PInC or IY?
2. Can sufficient numbers of families be (a) recruited and (b) retained such that a full‐scale RCT is likely to be feasible?
3. Are research procedures and measures feasible and acceptable to participating families?

## Study Design

A randomised controlled feasibility trial. The intervention will be delivered in four waves. Participants of waves 1, 2 and 3 will have follow up assessments after 12 months, participants of wave 4 will have follow-up assessments after 6 months.

## Randomisation

Families will be randomised 1:1 to receive either PInC or IY. No stratification or minimisation is applied.

## Sample Size and Power

In an unfunded previous evaluation there were 462 children referred to PInC in 4 years in Fife, with 228 (49%) attending at least the first session. In funded intervention studies in similar populations, response and retention rates have been higher. On this basis, the aim will be to approach 100 eligible participants over 7-12 months. Assuming a 60% response rate and two-thirds retention, this will result in 20 families in each intervention arm.

## Interim Analyses and Stopping Rules

There are no planned interim analyses or stopping rules in this trial.

## Study Population

### Inclusion criteria

Parents of children aged 5-12 with a formal diagnosis of ADHD, following a standardised assessment from a paediatrician or a psychiatrist through the Fife integrated ADHD pathway during the one-year recruitment period.

### Exclusion criteria

1. Family attending other parenting groups.
2. Inability to complete questionnaires or participate in groups because of limited English language comprehension.
3. Participants already taking part in research on a parenting intervention.

## Feasibility Outcomes

The outcomes related to feasibility are

- Consent rate among all families that were approached;
- Retention rate among all consenting families;
- Completeness of the putative outcome measures for a full trial.

## Proposed Efficacy Outcomes

### Primary Outcome

The proposed primary outcome for a full trial is the parental sense of competence, measured by the Parental Sense of Competence Scale (PSOC).

### Secondary Outcomes

The proposed secondary outcomes for a full trial are

- Eyberg Child Behaviour Inventory (ECBI) problem score > 11 / intensity score > 127
- Strength and Difficulties Questionnaire (SDQ) total score
- General Health Questionnaire (GHQ)
- Parental ADHD symptoms measured using the ADHD Rating Scale (ASRS-v1.1) Part A and Part B
- Parenting stress measured using the Parenting Daily Hassles Scale (PDHS) challenging behaviour intensity and frequency , parenting tasks frequency and intensity
- Goal Based Outcomes from the Child Outcomes Research Consortium (CORC-GBO) – amount of movement along the scale from baseline to follow-up
- Parent quality of life measured using the EQ-5D-5L (health utility score and VAS)
- Child quality of life measured using the PedsQL total score, psychosocial health summary score, physical health summary score
- Service use

## Statistical Analysis Plan (SAP)

### SAP Objectives

The objective of this SAP is to describe the statistical analyses to be carried out for the SPARCLAR study.

### General Principles

Rates will be calculated with Clopper-Pearson^1^ 95% confidence intervals.

Proposed primary and secondary outcome measures will be summarised at baseline and follow up, and separately by follow-up time point (12 months for recruitment waves 1 to 3, 6 months for recruitment wave 4). Changes from baseline in the proposed outcome measures will be summarised in the same way. All summaries will include the number of observed values and the number of missing values. Continuous variables will be summarised by the mean, standard deviation, median, interquartile range, minimum and maximum. Categorical variables will be summarised as the number and percentage of participants in each group.

The primary and numeric secondary efficacy outcomes will be compared between intervention groups using linear regression analyses predicting change in outcome from intervention group, adjusting for baseline value of the outcome, age and gender.

Binary secondary efficacy outcomes will be compared between intervention groups using logistic regression analyses predicting outcome from intervention group, adjusting for age and gender.

If numbers are too low for the planned regression analysis, unadjusted regression analyses or simple tests will be carried out instead. For numbers below five in any group, no statistical tests will be carried out.

The distribution of the residuals of each linear regression analysis will be reviewed and transformations will be applied to the outcome variable as appropriate.

Regression results will be reported as adjusted mean difference between intervention groups, or adjusted odds ratios for logistic regressions, with 95% confidence interval and p-value.

Missing values will not be imputed.

Health economic analyses will be carried out by health economists and are not part of this SAP.

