## Safety Outcomes

### Treatment Compliance

Group attendance will be summarised overall and by intervention group.

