| Change from baseline | Mean (SD)  Median (IQR)  [Range] | xx.x (xx.x)  xx.x (xx.x, xx.x)  [xx.x, xx.x] | xx.x (xx.x)  xx.x (xx.x, xx.x)  [xx.x, xx.x] | xx.x (xx.x)  xx.x (xx.x, xx.x)  [xx.x, xx.x] |
| Linear regression analysis predicting change from baseline from randomised intervention group adjusting for baseline PSOC, child age and gender | | | | |
|  |  | Adjusted mean difference (95% confidence interval) | | p-value |
| IY vs. PInC | | x.xx (x.xx, x.xx) | | x.xxxx |
| Residual standard deviation | | x.xx | |  |

Table 3.2 Primary outcome - PSOC. ITT population with 12-month follow-up.

|  |  |  | Randomised intervention | |
| --- | --- | --- | --- | --- |
|  |  | All | PInC | IY |
| Baseline | N_OBS_ (N_MISS_)  Mean (SD)  Median (IQR)  [Range] | nn (nn)  xx.x (xx.x)  xx.x (xx.x, xx.x)  [xx.x, xx.x] | nn (nn)  xx.x (xx.x)  xx.x (xx.x, xx.x)  [xx.x, xx.x] | nn (nn)  xx.x (xx.x)  xx.x (xx.x, xx.x)  [xx.x, xx.x] |
| Follow-up | N_OBS_ (N_MISS_)  Mean (SD)  Median (IQR)  [Range] | nn (nn)  xx.x (xx.x)  xx.x (xx.x, xx.x)  [xx.x, xx.x] | nn (nn)  xx.x (xx.x)  xx.x (xx.x, xx.x)  [xx.x, xx.x] | nn (nn)  xx.x (xx.x)  xx.x (xx.x, xx.x)  [xx.x, xx.x] |
| Participants with baseline and follow-up data only | | | | |
| N |  | nn | nn | nn |
| Baseline | Mean (SD)  Median (IQR)  [Range] | xx.x (xx.x)  xx.x (xx.x, xx.x)  [xx.x, xx.x] | xx.x (xx.x)  xx.x (xx.x, xx.x)  [xx.x, xx.x] | xx.x (xx.x)  xx.x (xx.x, xx.x)  [xx.x, xx.x] |
| Follow-up | Mean (SD)  Median (IQR)  [Range] | xx.x (xx.x)  xx.x (xx.x, xx.x)  [xx.x, xx.x] | xx.x (xx.x)  xx.x (xx.x, xx.x)  [xx.x, xx.x] | xx.x (xx.x)  xx.x (xx.x, xx.x)  [xx.x, xx.x] |
| Change from baseline | Mean (SD)  Median (IQR)  [Range] | xx.x (xx.x)  xx.x (xx.x, xx.x)  [xx.x, xx.x] | xx.x (xx.x)  xx.x (xx.x, xx.x)  [xx.x, xx.x] | xx.x (xx.x)  xx.x (xx.x, xx.x)  [xx.x, xx.x] |
| Linear regression analysis predicting change from baseline from randomised intervention group adjusting for baseline PSOC, child age and gender | | | | |
|  |  | Adjusted mean difference (95% confidence interval) | | p-value |
| IY vs. PInC | | x.xx (x.xx, x.xx) | | x.xxxx |
| Residual standard deviation | | x.xx | |  |

Table 3.3 Primary outcome - PSOC. PP population.

|  |  |  | Intervention received | |
| --- | --- | --- | --- | --- |
|  |  | All | PInC | IY |

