| Proportion of sessions attended (%) | N_OBS_ (N_MISS_)  Mean (SD)  Median (IQR)  [Range] | nn (nn)  xx.x (xx.x)  xx.x (xx.x, xx.x)  [xx.x, xx.x] | nn (nn)  xx.x (xx.x)  xx.x (xx.x, xx.x)  [xx.x, xx.x] | nn (nn)  xx.x (xx.x)  xx.x (xx.x, xx.x)  [xx.x, xx.x] |

Table 5.2 Attendance at group sessions by sessions – PinC

| Session | Number not withdrawn | Number attended | Percentage attended |
| --- | --- | --- | --- |
| Week 1 | nn | nn | xx.x |
| Week 2 | nn | nn | xx.x |
| Week 3 | nn | nn | xx.x |
| Week 4 | nn | nn | xx.x |
| Week 5 | nn | nn | xx.x |
| Follow-up | nn | nn | xx.x |
| Attended at least 2 sessions | nn | nn | xx.x |

Table 5.3 Attendance at group sessions by sessions – IY

| Session | Number not withdrawn | Number attended | Percentage attended |
| --- | --- | --- | --- |
| Week 1 | nn | nn | xx.x |
| Week 2 | nn | nn | xx.x |
| Week 3 | nn | Nn | xx.x |
| Week 4 | nn | Nn | xx.x |
| Week 5 | nn | Nn | xx.x |
| … | … | … | … |
| Week 14 | nn | Nn | xx.x |
| Attended at least 7 sessions | nn | Nn | xx.x |

Table 6.1 Withdrawals from the intervention

|  |  |  | Randomised intervention | |
| --- | --- | --- | --- | --- |
|  |  | All | PInC | IY |
| Withdrawals | N_OBS_ (N_MISS_)  N(%) No  N(%) Yes | nn (nn)  nn (xx.x)  nn (xx.x) | nn (nn)  nn (xx.x)  nn (xx.x) | nn (nn)  nn (xx.x)  nn (xx.x) |
| Withdrawal reasons | N_OBS_ (N_MISS_)  N(%) Wished to attend another intervention  N(%) Didn’t want to continue  N(%) Couldn’t attend due to ill health  N(%) time commitment  N(%) No reason given | nn (nn)  nn (xx.x)  nn (xx.x) | nn (nn)  nn (xx.x)  nn (xx.x) | nn (nn)  nn (xx.x)  nn (xx.x) |

Table 6.2 Withdrawals from the study

|  |  |  | Randomised intervention | |
| --- | --- | --- | --- | --- |
|  |  | All | PInC | IY |
| Withdrawals | N_OBS_ (N_MISS_)  N(%) No  N(%) Yes | nn (nn)  nn (xx.x)  nn (xx.x) | nn (nn)  nn (xx.x)  nn (xx.x) | nn (nn)  nn (xx.x)  nn (xx.x) |
| Withdrawal reasons | N_OBS_ (N_MISS_)  N(%) Unhappy with baseline questionnaire  N(%) Too busy  N(%) Did not attend baseline assessment… | nn (nn)  nn (xx.x)  nn (xx.x)  nn (xx.x) | nn (nn)  nn (xx.x)  nn (xx.x)  nn (xx.x) | nn (nn)  nn (xx.x)  nn (xx.x)  nn (xx.x) |

Table 7 Summary of adverse events

|  |  |  | Randomised intervention | |
| --- | --- | --- | --- | --- |
|  |  | All | PInC | IY |
| Participants experiencing at least one SAE | N(%) | nn (xx.x) | nn (xx.x) | nn (xx.x) |
| Number of events | N | nn | nn | nn |

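### Both programmes are delivered in groups, but every planned comparison treats families as independent and no intraclass correlation is reported

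*Supplement*

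**What the plan says.** On delivery, the SAP's Study Design section states: "The intervention will be delivered in four waves". Both arms meet as groups. Under Treatment Compliance, "Group attendance will be summarised overall and by intervention group", and the Table Templates include "Table 5.2 Attendance at group sessions by sessions – PinC" (five weekly sessions and a follow-up session) and "Table 5.3 Attendance at group sessions by sessions – IY" (14 weeks). The SAP does not state how many groups run in each arm or wave, or how large they are.

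On allocation, the Randomisation section states: "Families will be randomised 1:1 to receive either PInC or IY", and "No stratification or minimisation is applied". Families are therefore allocated individually, and the grouping arises afterwards, in both arms.

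On analysis, General Principles states: "The primary and numeric secondary efficacy outcomes will be compared between intervention groups using linear regression analyses predicting change in outcome from intervention group". The sections on the putative primary and secondary outcomes give the same covariates: baseline value, child age and gender. The two ECBI cut-offs are analysed by logistic regression with the matching covariates. The 12-month, repeat-baseline and per-protocol analyses reuse these models. If numbers are small, the fallback is a regression without covariates or an elementary test. Templates 3.1 to 3.3 report the adjusted difference, its 95% interval, the p-value and the "Residual standard deviation". The SAP nowhere mentions clustering, a group or wave effect, robust standard errors, a design effect or an ICC. Protocol version 5 is not shown, but the SAP declares no planned departure from the protocol's analyses.

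**The concern.** Families who attend the same course meet the same peers and share the same sessions, so their outcomes may be more alike than those of families in other groups. Ordinary regression counts each family as a separate piece of information. With positive within-group correlation, it understates the standard error of the arm comparison, and this carries into the intervals and p-values that the SAP commits to reporting.

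The second stake is planning. A full trial of two group-delivered programmes needs a group size and an ICC as well as a standard deviation. The feasibility trial is a natural place to record the first and make a rough estimate of the second, and the SAP plans neither.

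**Working it through.** **The plan's own figure.** Sample Size and Power assumes 100 approached, 60% response and two-thirds retention: 100 × 0.60 = 60; 60 × 2/3 = 40; 40 / 2 = 20 per arm. This reproduces. It is a recruitment projection with no effect size, SD or power, so there is no power figure to correct.

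**Assumed group layouts.** One group per arm per wave gives 4 × 2 = 8 groups of 40 / 8 = 5 followed-up families. Alternatively, 2 groups per arm give 4 groups of 40 / 4 = 10. The ICC is also assumed: it is the correlation left within a group after the model's covariates.

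**Formulas.** Design effect DE = 1 + (m − 1) × ICC, with m families per group. The true standard error is √DE times the one the independence model reports. The false-positive rates come from simulating the planned model (arm, baseline, age and gender; two-sided 5% test) with no true difference.

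| Layout | ICC | DE | √DE | False-positive rate |
|---|---|---|---|---|
| 8 groups of 5 | 0 | 1.00 | 1.00 | about 5% |
| 8 groups of 5 | 0.02 | 1 + 4 × 0.02 = 1.08 | 1.04 | about 6% |
| 8 groups of 5 | 0.05 | 1 + 4 × 0.05 = 1.20 | 1.10 | about 7% |
| 8 groups of 5 | 0.10 | 1 + 4 × 0.10 = 1.40 | 1.18 | about 9.5% |
| 4 groups of 10 | 0.02 | 1 + 9 × 0.02 = 1.18 | 1.09 | about 7% |
| 4 groups of 10 | 0.05 | 1 + 9 × 0.05 = 1.45 | 1.20 | about 10% |
| 4 groups of 10 | 0.10 | 1 + 9 × 0.10 = 1.90 | 1.38 | about 16% |

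A t-test without covariates (40,000 simulated trials per setting) agrees. At ICC 0.05 and 0.10 it gives 7.3% and 10.2% for 8 groups, and 10.4% and 16.1% for 4 groups.

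**Planning illustration.** All inputs are assumed: standardised difference 0.4, 80% power, two-sided 5%, groups of 8. Without clustering, 99 families per arm are needed. At ICC 0.01: 99 × 1.07 = 105.9, so 106. At 0.05: 99 × 1.35 = 133.7, so 134. At 0.10: 99 × 1.70 = 168.3, so 169.

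**How well this trial could estimate an ICC.** With a true ICC of 0.05 and 8 groups of 5, the central 95% of simulated estimates runs from about −0.18 to 0.34, and 42% are zero or below.

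**The case against.** Most of the case on the other side limits the point without removing it.

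- *The harm is conditional.* A reader might infer that the intervals are certainly too narrow. The documents do not support this: they give no ICC and no group size. At ICC 0 there is no loss, and at 0.01 with groups of 5 the design effect is only 1.04. This stands.
- *Not every followed-up family is exposed to a group.* In the earlier evaluation that the SAP cites, 228 of 462 referred children (49%) had a family at the first session, and the intention-to-treat set requires no attendance. Families who never attend share no group, so the effective cluster is smaller. This stands for the intention-to-treat analysis. It has less force per protocol, where a minimum attendance is required.
- *The residual SD is not the fault.* A reader might infer that it is the wrong quantity because it mixes variation between and within groups. In fact it approximates the total adjusted SD to which a design effect is applied. Only the ICC and the group sizes are missing.
- *Nothing says that the full trial will be sized without an ICC.* Its planners may take one from elsewhere. This also stands: under-sizing is a risk, not a stated plan.
- *The efficacy results decide nothing here.* The research questions concern willingness to be randomised, recruitment, retention and acceptability. The consent, retention and completeness proportions do not use these regressions. This lowers the weight of the point, but the SAP still commits to intervals and p-values for efficacy.
- *A mixed model is costly with so few groups.* With about 6 group-level degrees of freedom against 35, the t multiplier rises from 2.03 to 2.45, about 21%, even at ICC 0. When the estimated group variance is zero, the point estimate and model-based standard error return to those of the planned regression. This is a good reason not to make it the main analysis, but no reason to leave it out as a sensitivity analysis.

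**Conclusion.** The omission is a matter of record: both arms are group-delivered, every comparison and the fallback assume independence, and no ICC is planned. The consequence is conditional. For a positive ICC between 0.02 and 0.10, the planned standard errors are understated by a factor of 1.04 to 1.18 with 8 groups of 5, or 1.09 to 1.38 with 4 groups of 10. False-positive rates are then about 6% to 9.5%, or 7% to 16%, against a nominal 5%. These figures rest on assumed group numbers and ICCs, and on all followed-up families belonging to a working group; they shrink where families never attended.

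The documents do not support the stronger conclusion that the planned regression must be replaced. The comparisons are exploratory, carry no power claim, and leave the feasibility outcomes untouched. This is an inexpensive improvement to the honesty of the efficacy intervals and to the information passed to the full trial.

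**What to change.** 1. Record each family's assigned delivery group and wave, and report the number and size of groups in each arm.
2. Keep the planned regression as the main exploratory analysis, and state beside its results that the intervals assume no clustering by delivery group.
3. Add a sensitivity analysis for PSOC and the continuous secondary outcomes: the same covariates plus a random intercept for assigned delivery group in both arms, fitted by REML with Kenward-Roger or Satterthwaite degrees of freedom. Using the assigned group places families who attended no session; add a rule for any family never given a group. Template 3.3 is laid out by intervention received, so state there which group defines the cluster.
4. Add the ICC with its 95% confidence interval beside the residual SD in Tables 3.1 to 3.3, with a note that it should not be used alone to size the full trial.

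The cost is a group identifier, which attendance registers should already hold, a few sentences in the SAP and one row in three tables. The drawbacks are wider intervals in the sensitivity analysis and a very imprecise ICC that will often be estimated as zero.

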## Efficacy Outcomes

### Putative Primary Outcome

Change from baseline in PSOC will be analysed in a linear regression analysis predicting change from baseline from randomised intervention group adjusting for baseline PSOC, child age and gender.

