### Putative Secondary outcomes

Change from baseline in each continuous secondary outcome measure will be analysed in a linear regression analysis predicting change from baseline from randomised intervention group adjusting for baseline value of the outcome measure, child age and gender.

Binary secondary outcome measures (ECBI problem score > 11 and ECBI intensity score > 127) will be analysed in a logistic regression analysis predicting the outcome from randomised intervention group adjusting for baseline ECBI problem score or ECBI intensity score (as continuous measures), child age and gender.

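### The low-numbers fallback in SAP General Principles goes straight to unadjusted analyses; it should drop child age and gender first and keep the baseline score

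*Supplement*

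**What the plan says.** For continuous outcomes, SAP General Principles plans a linear regression of change on intervention group, "adjusting for baseline value of the outcome, age and gender". The Putative Primary Outcome section repeats this for PSOC, "adjusting for baseline PSOC, child age and gender".

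General Principles then gives the fallback: "If numbers are too low for the planned regression analysis, unadjusted regression analyses or simple tests will be carried out instead". The next sentence sets a floor: "For numbers below five in any group, no statistical tests will be carried out". The SAP gives no number for when the fallback starts, no order for removing covariates, and no penalised or exact method.

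For the binary ECBI outcomes the SAP describes three different models:

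- General Principles has no baseline term: "logistic regression analyses predicting outcome from intervention group, adjusting for age and gender".
- Putative Secondary Outcomes adds the score itself: "adjusting for baseline ECBI problem score or ECBI intensity score (as continuous measures), child age and gender".
- The shell for Table 4.1.1 adjusts for baseline problem score as a dichotomy at 11.

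On size, "the aim will be to approach 100 eligible participants over 7-12 months". With 60% response and two-thirds retention, the Sample Size section expects 20 families per arm. Missing values are not imputed. The analyses are repeated in families with 12-month follow-up only, and the primary outcome is repeated in the per-protocol population.

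**The concern.** The fallback removes every covariate at once, including the most useful one. In an unstratified trial, chance imbalance in the baseline score grows as the groups shrink, so the protection is withdrawn where it is most needed.

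An unadjusted analysis of change does not make up for this. Subtracting baseline is not the same as adjusting for it. When one arm starts higher, regression to the mean makes its average change look smaller, and that difference enters the estimate.

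For a binary outcome, the unadjusted odds ratio is also a different quantity from the adjusted one, while the reporting rule and the table shells are labelled as adjusted.

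At stake are the precision of the exploratory estimates and their comparability between the main and 12-month tables (and the per-protocol table for PSOC). The residual SD shown in the PSOC tables is affected too. No confirmatory conclusion depends on this.

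**Working it through.** **Plan's own figure.** 100 × 0.60 × 2/3 = 40 families, or 20 per arm. This reproduces. The SAP gives no power, effect size or SD to check.

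**Chance baseline imbalance.** With *n* per arm, the between-arm difference in mean baseline has SD √(2/n) in baseline SD units. The probability that it exceeds 0.5 SD in either direction follows from the normal distribution.

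| n per arm | SD of difference | P(above 0.5 SD) |
|---|---|---|
| 20 | 0.32 | 11% |
| 15 | 0.37 | 17% |
| 10 | 0.45 | 26% |
| 5 | 0.63 | 43% |

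Fifteen per arm is roughly the 12-month set if the four waves are equal in size, which is an assumption.

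**Linear outcomes: precision.** Let r be the baseline/follow-up correlation, with equal SDs. Change has variance 2(1 − r). After adjustment for baseline the residual variance is 1 − r². The large-sample ratio of interval widths is therefore √(2/(1 + r)), which is 1.24, 1.15 and 1.08 at r = 0.3, 0.5 and 0.7. Small samples give some of this back through the lost degree of freedom and the imbalance itself, so the widths were simulated (4,000 trials per cell, no arm effect; age and gender unrelated to outcome).

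| n per arm | r | Mean 95% CI width, unadjusted | Baseline only | Ratio |
|---|---|---|---|---|
| 10 | 0.3 | 2.186 | 1.818 | 1.20 |
| 10 | 0.5 | 1.856 | 1.660 | 1.12 |
| 10 | 0.7 | 1.435 | 1.366 | 1.05 |
| 5 | 0.3 | 3.315 | 2.930 | 1.13 |
| 5 | 0.5 | 2.824 | 2.670 | 1.06 |
| 5 | 0.7 | 2.197 | 2.228 | 0.99 |

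**Linear outcomes: shift.** Given a baseline difference d, the unadjusted change estimate is displaced by (r − 1)d. In simulated trials with d above 0.5 SD, the mean displacement was −0.53, −0.40 and −0.21 SD at 10 per arm, and −0.60, −0.42 and −0.27 at 5 per arm (r = 0.3, 0.5, 0.7). With baseline kept it was within 0.03 of zero. As a check, at 5 per arm the mean of d given d > 0.5 is 0.86, so (r − 1)d gives −0.60, −0.43 and −0.26.

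**Why age and gender should go first.** At r = 0.5 and 5 per arm, the full planned model has a mean width of 3.41, against 2.67 with baseline only and 2.82 unadjusted. About 6% of simulated trials could not fit the full model (222 of 4,000). At 20 per arm the full model costs little: 1.15 against 1.12.

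**Binary ECBI outcomes: separation.** The SAP gives no share of families above the cut-offs, so 50% to 75% is assumed, with correlation 0.6 to 0.8. Separation of the model with arm, continuous baseline, age and gender was checked by linear programming:

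| Families | Separation, approximate range |
|---|---|
| 40 | 0–10% |
| 30 | 5–30% |
| 20 | 24–61% |

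The upper ends belong to 75% above the cut-off. At 50–60%, separation with 40 families is about 0–3%. Simulation runs differ by a few percentage points.

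**Binary ECBI outcomes: alternative.** This used a separate, milder scenario (log-odds 1.5 per baseline SD, intercept 0.5, 75% boys; 1,500 trials per size, no arm effect).

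| n per arm | Planned model fails or separates | Firth, arm and baseline, fails |
|---|---|---|
| 20 | 1.8% | 0.0% |
| 10 | 27.9% | 0.1% |
| 5 | 86.0% | 0.5% |

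In trials with baseline imbalance above 0.5 SD, the unadjusted log odds ratio was displaced by 0.78 at 10 per arm and 0.72 at 5. Firth with baseline gave −0.08 and −0.05. Its Wald test rejected in 1.0% or fewer of null trials at 10 per arm and below, so Wald intervals are too conservative there.

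**The case against.** **The fallback may never be used for the linear models.** At the planned 40 families a model with five coefficients fits. A reader might take the width penalty at 40 families (about 22%, 14% and 7% at the three correlations) as the cost of this rule, but the fallback would not apply there. The relevant figures are those at low numbers, and they are smaller.

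**Separation need not be common.** A reader might infer that the ECBI models will often fail at the planned size. The documents give no prevalence to support that. At 40 families the rate is near 10% only if about 75% are above the cut-off. Baseline is not always the main cause either: at correlation 0.6, removing it barely changes the separation rate (7.75% to 7.5% with 40 families), because sparse cells do most of the damage.

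**What the fallback drops is unclear for the binary outcomes.** General Principles has no baseline term in its logistic model, so baseline is lost only relative to the model under Putative Secondary Outcomes.

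**Unadjusted estimates are not biased.** Over repeated randomisation they are unbiased. The shift is conditional on the imbalance that occurs.

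**The switch is not stated to follow model failure.** The SAP's trigger is numbers. It is fair to say only that, without a threshold, the choice can be made after the data are seen.

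**Scope.** The per-protocol analysis covers the primary outcome only, so no per-protocol ECBI table is affected. The research questions concern willingness to be randomised, recruitment, retention and acceptability.

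All of these points stand and limit the finding. None gives a reason to discard baseline in the linear fallback.

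**Conclusion.** The concern holds for the linear outcomes. The fallback has no step that keeps baseline, and adding one costs almost nothing. At 10 per arm it avoids an interval about 5% to 20% wider. At 5 per arm the gain is about 13% and 6% at correlations 0.3 and 0.5 and nil at 0.7. At both sizes it removes a shift of about 0.2 to 0.6 SD in trials with a baseline imbalance above 0.5 SD.

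For the binary ECBI outcomes it holds in a narrower form. The three descriptions of the model must be reconciled. A penalised model is then a better fallback than an unadjusted one where numbers are low. Separation becomes a practical problem at about 20 to 30 families, not reliably at 40.

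The size rests on assumed correlations (0.3–0.7 linear, 0.6–0.8 binary) and an assumed 50–75% above the ECBI cut-offs. None of these is in the documents. Because the comparisons are putative in a feasibility trial, this is a minor-to-moderate improvement.

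**What to change.** In SAP General Principles:

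1. State, as a number per arm fixed before the data are seen, when numbers count as too low.
2. For linear outcomes, below that number drop child age and gender and keep the baseline value, down to the existing floor of five per group.
3. For the binary ECBI outcomes, make General Principles, Putative Secondary Outcomes and the Table 4.1.1 shell agree on whether and how baseline enters. Then, where the planned model separates or numbers are low, use Firth logistic regression with arm and continuous baseline score, with profile penalised-likelihood intervals, in place of the unadjusted model.
4. Name the fitted model under each table, so that the main and 12-month results can be compared.

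The cost is a few sentences of SAP text, one degree of freedom for baseline, and some shrinkage of the odds ratios. Firth regression makes the model estimable but adds no information, so intervals at these sizes will stay wide. No new data are needed.
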